#### Efficacy of the Therap-i module

The following analysis strategy will be applied to both primary (IDS-SR) and secondary outcomes (OQ-45, IPQ-MH subscales, and WAI-SR). The data have a two-level hierarchical structure, because multiple assessments are clustered within subjects. Therefore, multilevel regression analyses will be used to estimate fixed effects for time, treatment allocation, and their interaction, as well as random intercepts and a random slope for time. In this way, we can examine the effect of time on outcomes (across multiple outcome measurements), the effect of group (2 levels: experimental or control group), and the interaction between time and group separately. Thresholds for statistical significance will be set at *p* < 0.05.

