**Daily assessments**										
ESM^b^	momentary affect and other factors			−5 times a day-						
Actigraphy	physical activity			-continuous-						
**Evaluation Therap-i module**^b^										
Questionnaire	participant evaluation						X			
Questionnaire	clinician evaluation					X				
Interview	participant evaluation						X			

Note: P, pre-baseline; T0, baseline measurement; T1 till T7, follow-up waves (see method section for details); *CTQ-SF* Childhood Trauma Questionnaire Short Form, *DAS-A-17* Dysfunctional Attitude Scale form A, *DM-TRD* Dutch Method for quantification of Treatment Resistance in Depression, *ESM* Experienced Sampling Method, *IDS-SR* Inventory Depressive Symptomatology - Self-Report, *IPQ-MH* Illness Perception Questionnaire Mental Health, *LEIDS-RR* Leiden Index of Depression Sensitivity 2nd Revision, *Mini-SCAN* Mini-Schedules for Clinical Assessment in Neuropsychiatry, *OQ-45* Outcome Questionnaire-45, *QSRD* Questionnaire Self-management in Recovery of Depression, *TAS-20* Toronto Alexitymia Scale-20, *WAI-SR* Work Alliance Inventory Short form Revised. ^a^, WAI-SR is assessed at baseline if the patient already knows their clinician (see method section for details); ^b^ = experimental group only

Outcomes are assessed at all waves with the: i) Inventory of Depressive Symptomatology Self-Report (IDS-SR) to assess depression symptom severity [34–36]; ii) the Outcome Questionnaire (OQ-45) to assess changes in psychosocial functioning within three domains, including symptom distress, interpersonal functioning and social role [37, 38]; iii) Working Alliance Inventory – Short form Revised (WAI-SR) to assess therapeutic alliance between a patient and their clinician [39, 40]; and iv) Illness Perception Questionnaire Mental Health (IPQ-MH) to assess a patients’ perception of their illness with four of its sub-scales, namely, personal control over the problem, control gained in treatment, coherence, and emotional representation [41].

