### Statistical methods

#### Sample size calculation and withdrawal

We performed a sample size calculation for our main hypothesis that adding the Therap-i module to TAU will lead to greater reduction of depressive symptoms (as assessed with the IDS-SR) compared to TAU (G*Power 3.1, F test for repeated measures, within-between interactions [55]. Our power analysis is based on the effect size found in a previous study by Kramer and colleagues [21]. In their pioneer RCT, the authors showed that systematic intensive self-monitoring and personalized feedback on contextualized patterns of positive affect through ESM could provide an effective add-on tool to routine clinical care. IDS-SR scores for the experimental group showed an initial 3-point drop 7 weeks after baseline. While this effect became larger at later measurements, we chose the 7-week measurement as a reference point because it was the smallest post-intervention effect and therefore provided a conservative basis for the power analysis. Given a range of standard deviations of 10.0–10.5, the decrease in IDS-SR scores translates to an effect size of 0.14–0.15 (Cohen’s f). With a sample size of 80 (40 per group), an alpha of 0.05 and an intraclass correlation of 0.5 (between the pre and post repeated measures), and 4 measurement occasions (T0-T3), we have an 85–90% power to detect such an effect. To achieve a realistic estimation of the required sample size, one needs to further account for dropout. In a study from our department that is closely related to the proposed study [22, 23], dropout in the intervention period was 20%. Accordingly, to ensure that we will have at least 40 participants in each treatment arm, we will enrol 50 participants per study arm (total *n* = 100).

Patients can withdraw from the study at any time for any reason if they wish to do so without any consequences. In the case of withdrawal, attempts will be made to follow-up with the patient to establish cause of withdrawal, and to collect qualitative data regarding experience of participation. All data, including those from withdrawn patients (unless they request for their data to be deleted), will be included in the final analysis. If a patient withdraws from the study prematurely without providing valuable data, a replacement participant will be sought if resources allow. In case patients withdraw before randomization, they will be replaced. After randomization they will not be replaced.

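### The efficacy model gives each arm its own T0 level and reports a separate group effect; a common T0 mean, or T0 as a covariate, would be more precise at no cost

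*Protocol article*

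**What the plan says.** Under Efficacy of the Therap-i module, the article states that "multilevel regression analyses will be used to estimate fixed effects for time, treatment allocation, and their interaction, as well as random intercepts", plus a random slope for time. The purpose given is to look at time, at "the effect of group (2 levels: experimental or control group), and the interaction between time and group separately". One threshold applies ("Thresholds for statistical significance will be set at" p < 0.05), and the same strategy covers the primary and all secondary outcomes. The section mentions neither a baseline covariate nor a constraint on the arms at T0. It does not list the waves that enter the model or say how time is coded.

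Under Sample size calculation and withdrawal, the main hypothesis is a greater fall in IDS-SR with the module. It is powered with an "F test for repeated measures, within-between interactions", using "4 measurement occasions (T0-T3") and "an intraclass correlation of 0.5 (between the pre and post repeated measures"). T0 is therefore one of the repeated occasions in the design that was powered.

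Table 2 shows IDS-SR, OQ-45 and IPQ-MH at T0 through T7. The text below it says "Outcomes are assessed at all waves with the" four instruments, but the table's footnote limits WAI-SR at T0 to patients who already know their clinician.

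**The concern.** Allocation is randomised 1:1, so the true difference between arms at T0 is zero. A model with T0 in the outcome vector and a free group term estimates that difference anyway. The interaction then compares changes from two separately estimated starting points, and the noise in the T0 difference passes into the treatment estimate. Fixing the T0 difference at its known value, or conditioning on the T0 score, removes part of that noise.

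The group term has a second problem. It stands beside the interaction under an efficacy heading and the same threshold, yet it answers no efficacy question. What it estimates depends on the coding of time, and under neither usual coding is it the treatment effect. The trial is small, and the article's Discussion warns that the heterogeneity of a pragmatic design may lower power, so precision available from data already collected is worth having.

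**Working it through.** **Inputs from the article:** 40 per arm, alpha 0.05, correlation 0.5, four occasions T0-T3, SD 10.0 to 10.5, a 3-point difference.

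**Assumptions added here:** equally spaced waves, complete data, SD 10, normal approximation. Compound symmetry applies unless a random slope is stated.

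**1. The plan's own figure.** f = (3/SD)/2 gives 0.150 at SD 10 and 0.143 at SD 10.5. For the within-between interaction, lambda = f² × N × m/(1 − rho), with 3 and 234 degrees of freedom.
- f = 0.14: lambda = 0.0196 × 80 × 4/0.5 = 12.54, power 0.851.
- f = 0.15: lambda = 0.0225 × 80 × 4/0.5 = 14.40, power 0.900.

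The stated 85-90% reproduces, and the powered term is the interaction.

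**2. T3 contrast, categorical time, no random slope.**
- Free T0 levels: variance = 2 × SD² × (1 − rho) × 2/n = 2 × 100 × 0.5 × 2/40 = 5.00, SE 2.24.
- Common T0 mean: variance = SD² × (1 − rho²) × 2/n = 100 × 0.75 × 2/40 = 3.75, SE 1.94.
- Ratio = (1 + rho)/2 = 0.75. It is 0.65 at rho 0.3 and 0.85 at rho 0.7.

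**3. Linear time, no random slope** (time 0, 1, 2, 3; mean 1.5; sum of squares 5; intercept and residual variance 50 each).
- Interaction variance, free group term: 2 × 50/(40 × 5) = 0.50 per wave². SE at T3 = 3 × √0.50 = 2.12.
- Group-term variance at T0: (2/40) × [50 + 50 × (1/4 + 1.5²/5)] = 4.25.
- Covariance of the two: −2 × 50 × 1.5/(40 × 5) = −0.75.
- Fixing the group term at zero multiplies the interaction variance by 1 − 0.75²/(0.50 × 4.25) = 0.735. SE at T3 = 2.12 × √0.735 = 1.82.
- Over rho 0.3 to 0.7 the ratio is 0.60 to 0.85.

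Power for a 3-point T3 difference goes from 0.27 to 0.34 (categorical) or from 0.29 to 0.38 (linear). This is a single contrast, not the 3-df test in step 1, so it does not correct the stated power.

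**4. With the planned random slope, T0-T3.** The article gives no slope variance, so a range is assumed. Entries are the ratio of interaction variance, common T0 mean over free.

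| Slope SD (points per wave) | Intercept-slope correlation −0.3 | 0 | +0.3 |
|---|---|---|---|
| 1 | 0.69 | 0.76 | 0.82 |
| 2 | 0.69 | 0.81 | 0.90 |
| 3 | 0.72 | 0.86 | 0.95 |

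The gain is therefore roughly 5% to 31%.

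**5. Linear slope over T0-T7** (eight equally spaced waves). The ratio is 0.79 with no random slope and about 0.75 to 1.00 over the same grid, so the gain is generally smaller.

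**6. What the group term estimates.**
- Time zero at T0: the T0 difference, whose true value is 0.
- Time centred: the average over waves. A constant 3-point post-baseline effect becomes (0 + 3 + 3 + 3)/4 = 2.25. A course of 0, 1, 2, 3 becomes 1.5, against 2.0 over T1-T3.

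**7. Error rate if either term could count as success.** With centred time the two estimates are uncorrelated: 1 − 0.95² = 9.75%. With time zero at T0 their correlation is −0.75/√(0.50 × 4.25) = −0.51, and simulation gives 9.0%.

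**The case against.** The planned model is conventional and valid. T0 enters through the time-by-group contrast, which is unbiased under randomisation and whose test holds its size. Keeping a main effect beside its interaction is ordinary practice. All of this stands: the fault is one of efficiency, and a reader who inferred that the baseline is thrown away or the analysis is invalid would go too far.

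A reader might also infer two competing efficacy tests with a type I error near 10%. The article does not support that. The sample-size section ties the main hypothesis and the power to the interaction, and no rule lets either term count as success. The passage may simply describe what the coefficients represent; it treats time in the same way, and nobody would call that an efficacy test.

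The 25% figure belongs to a model without a random slope, whereas the plan has one. It should not be turned into a saving of a third in sample size (1/0.75 = 1.33) for the planned analysis. T0 as a modelled outcome is an inference from the sample-size section and Table 2, and the exact meaning of the group term depends on unstated time coding.

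It could be said that baseline handling belongs in a statistical analysis plan. That carries less weight here, because the article does fix the model terms, and those terms include a free allocation effect.

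**Conclusion.** The point holds as an improvement in precision and specification. If T0 is among the outcomes, as the sample-size section and Table 2 indicate, the model spends information on a baseline difference known to be zero in expectation. The variance cost for the T0-T3 contrast is about 25% at the article's own correlation without a random slope, and roughly 5% to 31% with one. For a linear slope over T0-T7 it is generally smaller and may be negligible. These ranges rest on assumed slope variances, equal spacing, complete data, and a T0 score unaffected by allocation.

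The separate group effect should not be read as efficacy under either usual time coding. An error rate of 9-10% would arise only under an either-term success rule, which the article does not state.

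**What to change.** For IDS-SR, OQ-45 and the IPQ-MH subscales, do one of the following:
- keep T0 as an outcome with one mean common to both arms, group-by-post-baseline-time terms and no group main effect (with linear time, code T0 as zero); or
- use the T0 score as a covariate, with T1 onward as outcomes.

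Add a sentence to the efficacy section that carries the sample-size section through: efficacy is judged only on the post-baseline group contrast. Leave WAI-SR out of this change, since its T0 value exists only for patients who already know their clinician.

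The cost is a revised model statement. T0 is already collected for these outcomes and the article reports data collection as ongoing, so the change could be made before analysis.

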#### Users evaluation of the Therap-i module

The evaluations of the Therap-i module by patients and clinicians will be assessed in two ways: quantitatively, and qualitatively through semi-structured interviews in a subsample of patients (*n* = 20). The quantitative data will be presented using descriptive statistics (means and standard deviations). The qualitative analyses will be performed according to the validated Qualitative Analysis Guide of Leuven (QUAGOL) procedure [56].

## Discussion

The ongoing global digitalisation influences the possibilities to monitor and manage our health and behaviours, and holds potential to improve outpatient mental healthcare. While routine outcome monitoring is being used to evaluate and compare treatment outcomes and process variables [57], the use of more frequent repeated measurements to assess psychopathological complaints has been limited. Currently existing monitoring routines are not fully taking advantage of the potential of these repeated measurements to obtain a fine-grained view on triggers and perpetuating factors of psychopathology. ESM offers the possibility to bring relevant information from outpatients’ daily life into regular consultations, enhancing a systematic personalized characterization of a patient’s psychopathology. In order to fulfil its promise to support precision psychiatry, ESM monitoring needs to be implemented in clinical practice, become part of the treatment process, and allow for personalization [58]. Until now, personalized ESM monitoring during psychotherapeutic treatment has not been researched as a supportive tool and with our pragmatic RCT study we aim to fill this gap. The unique contribution of our study is the integration of personalized ESM into regular outpatient treatment for depression. Quantitative and qualitative outcome variables will be combined to examine the added value of the Therap-i module. Specifically, the use of qualitative methods complements interests in clinical practice, since recovery and empowerment of patients are concepts which are difficult to grasp with quantitative measures. Data collection has started and will continue for at least another year. In short, the intent of the Therap-i module is to support the case conceptualisation process by increasing insight in a patient’s complaints and motivating change in behaviour through informed treatment strategies. As such the module may advance treatment efficacy for depression and the quality and duration of recovery from depression.

The following potential challenges should be mentioned. First, when interpreting our results, we have to take into account the selection bias of who was willing to enrol in the study. Not all patients and clinicians will be able, or are motivated, to invest time and effort needed to successfully participate. However, enrolment will show an accurate impression of the level of adoption of the module in this particular sample in clinical practice. Second, the study tests a combination of potentially active components in the Therap-i module: focus on resilience (via the resilience interview), ESM monitoring, the feedback rapport, and the collaborative discussion of the feedback results. Clear conclusions about the active ingredients are not warranted and more research will be needed for detailed insight into this matter. However, through our, quantitative and specifically qualitative evaluation of the Therap-i module, we gather information on these separate components to aid further testing and development. Third, the trial is “pragmatic” because it is designed to fit into regular clinical practice, which involves some flexibility in the procedure (e.g., different types and dose of TAU, different centers and therapists, a range of different comorbidities). The resulting heterogeneity may reduce statistical power and hide a potential effect of the Therap-i module. However, the fact that the trial is pragmatic also is a testament to the possibility to implement the module in clinical practice. Fourth, in case we find evidence that the Therap-i module is effective and a valuable contribution to the treatment of MDD patients, the findings cannot be generalized to other patient groups without additional study. Fifth, future large-scale clinical implementation of the Therap-i module would likely differ from this study because ideally patients and clinicians are able to implement the module independently without involvement of a researcher. To this end, therapists need to be trained and intuitive software needs to be developed.^1^

Despite these limitations, the Therap-i study will provide valuable insights into the promise of personalized ESM and ESM-based feedback in clinical practice. Currently, it is acknowledged that severe depressive problems are seldom fully cured as residual complaints often remain and that those affected have life-long vulnerabilities for relapse [59]. For this reason, the ultimate ambition behind our Therap-i module is to contribute to putting patients “back into the driver’s seat” and relieving them from the feeling that their depression is overpowering their lives.

## Data Availability

Data collection is ongoing therefore data and materials are not available. As such, there are currently neither publications containing the results of this study already published nor manuscripts in which results are described submitted to any journal.

## Abbreviations

CTQ-SF: Childhood Trauma Questionnaire Short Form
DAS-A-17: Dysfunctional Attitude Scale (form A) revised
DM-TRD: Dutch Method for quantification of Treatment Resistance in Depression
EMA: Ecological Momentary Assessment
ESM: Experienced Sampling Methodology
IDS-SR: Inventory of Depressive Symptomatology Self Report
IPQ-MH: Illness Perception Questionnaire Mental Health
LEIDS-RR: Leiden Index of Depression Sensitivity - second revision
MDD: Major Depressive Disorder
METc: Medical Ethical Committee
Mini-SCAN: Mini-Schedules for Clinical Assessment in Neuropsychology
OQ-45: Outcome Questionnaire
PETRA: PErsonalized Treatment by Real-time Assessment
QSRD: Questionnaire of Self-management in the Recovery from Depression
RCT: Randomized Controlled Trial
REDCap: Research Electronic Data Capture software
RoQua: Routine Outcome and QUality Assessment
TAS-20: Toronto Alexithymia Scale
TAU: Treatment As Usual
UMCG: University Medical Center Groningen
WAI-SR: Working Alliance Inventory – Short form Revised
